### Study population

2.3

All students in grades 3–4 at the selected schools will be screened for individual eligibility according to the inclusion and exclusion criteria. A total of 400 students will be enrolled, with 200 allocated to the intervention group and 200 to the control group, allowing for potential attrition.

#### Sample size calculation

2.3.1

The primary outcome for sample size estimation was the Body Mass Index Standard Deviation Score (BMI-SDS). Due to the lack of previous studies on coarse-cereal interventions in this population, sample size was estimated based on prior research evaluating comprehensive interventions on obesity in primary school students. The calculations assumed 80% power (*β* = 0.20), a two-sided significance level of 0.05 (*α* = 0.05), standard deviation *σ* = 1.39, and effect size *Δ* 0.17. The resulting sample size was 180 students per school. Allowing for 10–20% attrition, the target enrollment per school was set at 190–200 students (18). The calculation formula used will be:

$$n=\frac{{\left(Z_{\alpha /2}+Z_{\beta }\right)}^{2}{\left(2\sigma^{2}\right)}^{2}[1+(m-1)\rho ]}{{\left(\mu_{1}-\mu_{2}\right)}^{2}}$$

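### The stated 180 students per school does not follow from the stated inputs, which give about 1,050 per arm before any design effect, so the 80% power claim is unsupported as written

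*Protocol article*

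**What the plan says.** The protocol article, section 2.3.1 (Sample size calculation), takes BMI-SDS as the sizing outcome and draws its inputs from earlier research on comprehensive obesity interventions. It gives the inputs in full: "The calculations assumed 80% power", "a two-sided significance level of 0.05", "standard deviation *σ* = 1.39" and "effect size *Δ* 0.17". It then reports "The resulting sample size was 180 students per school" and adds "Allowing for 10–20% attrition, the target enrollment per school was set at 190–200 students". The printed formula is a two-means formula with the squared difference in the denominator, a variance term written as (2σ²)², and a design-effect factor 1 + (m − 1)ρ. No value of ρ is given.

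Section 2.2 randomizes two schools, one to each arm. Section 2.3 confirms the allocation: "A total of 400 students will be enrolled, with 200 allocated to the intervention group and 200 to the control group". The per-school figure is therefore the per-arm figure. Section 2.6.2 plans a mixed model with the baseline value of the outcome as a covariate and school as a random effect.

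**The concern.** Inputs, formula and result are all printed in one paragraph, so the result can be checked directly. A difference of 0.17 against a standard deviation of 1.39 is about 0.12 of a standard deviation (0.17 / 1.39). An effect that small normally needs around a thousand participants per arm, and 180 is about one-sixth of that.

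The power statement governs how a null result will be read. If BMI-SDS shows no significant difference, readers will take it as evidence against an effect of 0.17 from a trial with 80% power. On the printed inputs, most trials of this size would miss that effect even if it were real. The article also links its findings to national student-meal policy (sections 3.3 and 4), so the misreading would matter.

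**Working it through.** **Inputs (section 2.3.1).** Two-sided alpha 0.05 (z = 1.960), power 80% (z = 0.842), σ = 1.39, Δ = 0.17. Then (1.960 + 0.842)² = 7.849, σ² = 1.9321, Δ² = 0.0289.

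**Step 1: try to reproduce 180, with the design effect set to 1 (its lowest value for ρ ≥ 0).**

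- Standard formula, n = 7.849 × 2σ² / Δ² = 7.849 × 3.8642 / 0.0289 = 1,049.5, so 1,050 per arm.
- Formula as printed, n = 7.849 × (2σ²)² / Δ² = 7.849 × 14.932 / 0.0289 ≈ 4,055.4, so 4,056 per arm.
- One-sided test: 827.
- One-sample or paired, with SD 1.39: 525 (one-sided 414).
- 0.17 read as a standardised effect: 544.
- 1.39 read as a variance: 756.

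None is close to 180. The only arithmetic found that lands nearby leaves the difference unsquared: 7.849 × 3.8642 / 0.17 = 178.4. That is a slip rather than a valid variant, and nothing in the article confirms that it happened.

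**Step 2: what 180 per arm delivers on the stated inputs (unadjusted, ICC = 0).**

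- Standard error = 1.39 × √(2/180) = 0.1465.
- Δ / SE = 0.17 / 0.1465 = 1.160, and power ≈ Φ(1.160 − 1.960) ≈ 21%. A noncentral t calculation also gives 21.2%. At 200 per arm it is 23%.
- Difference detectable with 80% power = 2.802 × 0.1465 = 0.41, which is 2.4 times the planned 0.17.
- The SD that would make 180 correct for Δ = 0.17 is about 0.58.

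**Step 3: allow for the planned baseline adjustment.** If 1.39 is a cross-sectional SD and r is the baseline–follow-up correlation, the residual variance is σ²(1 − r²). Reaching 180 needs 1 − r² = 180/1,050 = 0.171, so r ≈ 0.91. Power at 180 per arm with ICC = 0, for assumed values of r:

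| r | Power |
|---|---|
| 0.70 | 37% |
| 0.80 | 49% |
| 0.90 | 76% |
| 0.91 | 80% |
| 0.95 | 96% |

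The article states no r, and its formula has no such term.

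**Step 4: allow for clustering.** With one school per arm, the cluster size m equals the per-arm n. The unadjusted variance of the difference is 2σ²[1 + (n − 1)ρ]/n, which tends to 2σ²ρ as n grows and never falls below it. At an assumed ρ of 0.01:

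- Limiting SE = 1.39 × √0.02 = 0.197.
- Δ / SE = 0.865.
- Power, counting both tails, approaches but does not exceed about 14%, however many pupils are enrolled.

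Setting n = 1,049.5 × [1 + (n − 1)ρ] gives a positive solution only if ρ is below 1/1,049.5, about 0.001. These clustering figures treat ρ as known. With one school per arm the trial cannot separate the between-school variance from the intervention effect.

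**The case against.** The strongest objection is that the mismatch shows only that the inputs and the result do not fit together, not which of them is wrong. The SD and the difference come from earlier research that the article does not reproduce, and either could be misreported. The planned analysis also adjusts for baseline, and BMI-SDS may well be strongly correlated over a few months. This stands as a limit. A reader might infer that the trial's true power is 21%, and the document does not support that. The 21% is what the stated inputs imply for an unadjusted comparison with ICC = 0. The objection does not rescue 180, because the required correlation of about 0.91 and the zero ICC are nowhere stated.

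A reader might also multiply 1,050 by a design effect computed at a fixed cluster size of 180 and quote the product as the enrolment needed. That would assume many schools per arm. With one school per arm, adding pupils enlarges the same cluster, so no such target exists at an ICC of 0.01.

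Three further points carry less weight.

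- The squared variance term may be a typesetting slip. It raises n, so it cannot explain 180, and the finding does not depend on it.
- The missing ρ may be in a fuller protocol and is not treated here as a separate defect.
- Section 3.4 calls the trial a pilot, which tempers how a null result should be read. Section 2.3.1 nevertheless claims 80% power, and section 4 says the results will be robust and usable for policy.

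**Conclusion.** The stated size and power contradict the stated inputs. With two-sided alpha 0.05, 80% power, σ = 1.39 and Δ = 0.17, the requirement is about 1,050 per arm with no design effect, against 180 stated. The formula as printed gives about 4,056. The 80% power claim is therefore unsupported as written.

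The size of the shortfall depends on the analysis assumed. Unadjusted and with ICC = 0, 180 per arm gives about 21% power, or a detectable difference of about 0.41. With baseline adjustment and ICC = 0, power depends on an unstated correlation and reaches 80% only at r of about 0.91. Any ICC above zero lowers these figures. The mismatch itself rests only on the article's own numbers; the values of r and ICC used to show its range are assumptions.

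**What to change.** 1. Recheck σ, Δ and n against the source from which they were taken, and correct whichever was misreported.
2. Correct the printed variance term to 2σ².
3. Then take one of two routes:
   - Withdraw the 80% power claim and restate what 180 per school delivers: about 21% power for 0.17, or a detectable difference of about 0.41. Print the conditions (unadjusted, ICC = 0) beside the figure.
   - Alternatively, state the baseline correlation and residual SD that justify 180, and show power over r = 0.80 to 0.95 at ICC = 0.
4. Under either route, state that with one school per arm any ICC above zero lowers power further and cannot be overcome by enrolling more pupils in the same two schools. At an assumed ICC of 0.01, unadjusted power stays below about 14% at any enrolment.

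The cost is rewriting one paragraph, and the stated power may become less favourable. No extra enrolment is proposed, and the change can still be made although the study has started.

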### Randomization and allocation

2.2

Clusters, defined as individual schools, serve as the unit of randomization. The study population is drawn from public primary schools in Huairou District, Beijing, where the prevalence of overweight and obesity among school-aged children exceeds 30%, highlighting the need for effective interventions.

Eligible schools met the following criteria: (1) Availability of an on-site cafeteria capable of providing daily breakfast and lunch to ensure consistent implementation of coarse-cereal substitution; (2) No dietary intervention programs implemented in the past year; (3) Enrollment of at least 150 students in grades 3–4 (ages 8–12) to ensure sufficient sample size per cluster, and (4) Approval from school administrators to participate in the trial.

Two schools meeting these criteria will be randomly assigned to either the intervention or control group using a computer-generated random number table (SAS 9.4).

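### Enrolling 190–200 per school preserves the stated 180 only up to 5.3–10% attrition, not 10–20%, and the 150-pupil school floor does not secure 180 either

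*Protocol article*

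**What the plan says.** All references are to the protocol article.

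- **Section 2.3.1, required size.** "The resulting sample size was 180 students per school".
- **Section 2.3.1, attrition allowance.** "Allowing for 10–20% attrition, the target enrollment per school was set at 190–200 students".
- **Section 2.3, planned enrolment.** A total of 400 students, "with 200 allocated to the intervention group and 200 to the control group, allowing for potential attrition".
- **Section 2.2, school eligibility.** One criterion reads "Enrollment of at least 150 students in grades 3–4 (ages 8–12) to ensure sufficient sample size per cluster". Two schools that meet the criteria are randomised, so each arm is a single school.
- **Sections 2.3, 2.3.2 and 2.3.3, source of pupils.** Participants come only from grades 3–4 of the selected schools, after written parental consent and after health exclusions.

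**The concern.** Three numbers are meant to form a chain: the pupils a school must have, the pupils to enrol, and the pupils left after losses. Each link should be large enough to support the next.

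The enrolment range looks too small for the attrition it is said to absorb. The school floor is given a purpose, adequate size per cluster, yet it is smaller than the number the calculation requires.

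At stake is what a reader may believe about the trial's tolerance. The text says losses of up to 20% are covered. If they are not, an outcome inside the plan's own attrition range leaves fewer children than planned. With one school per arm, a shortfall in either school cannot be offset by recruiting elsewhere in that arm.

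**Working it through.** **Inputs.** Required number 180 per school; attrition 10–20%; target 190–200 per school (all section 2.3.1). Enrolment 200 per group (section 2.3). School floor 150 (section 2.2).

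**1. Trying to reproduce 190–200.** With attrition d, the number to enrol is 180/(1 − d).

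- d = 0.10: 180/0.90 = 200
- d = 0.20: 180/0.80 = 225

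The range should be 200–225 per school, or 400–450 in total. The common shortcut 180 × (1 + d) gives 198 and 216, so it does not yield 190–200 either. The printed range equals 180 plus 10 and 180 plus 20 pupils, as if percentages had been added as head counts. That is conjecture; the article does not say how the range was obtained.

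**2. Attrition that the printed range covers.** The tolerated loss is 1 − 180/N.

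- N = 190: 1 − 180/190 = 5.3%
- N = 200: 1 − 180/200 = 10.0%

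The only pairing that agrees with the text is 200 enrolled with 10% loss.

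**3. Numbers completing follow-up, per school.**

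| Starting number | 10% loss | 20% loss |
|---|---|---|
| 190 | 171 | 152 |
| 200 | 180 | 160 |
| 150 (school at the floor, every pupil eligible and consenting) | 135 | 120 |

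Against 180, the 20% column is short by 28/180 = 16% from 190 and by 20/180 = 11% from 200. From the floor, the shortfall is 45/180 = 25% at 10% loss and 60/180 = 33% at 20%.

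**4. The floor against the target.** 150 is below 180, so a school exactly at the floor misses the required number even with full consent and no losses. A school with 150–189 pupils cannot reach the lower end of the section 2.3.1 target (190). One with 150–199 cannot reach the 200 of section 2.3. The documents give no consent rate, so none is applied here; any refusals or exclusions lower these counts.

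**5. Is 180 itself a sound reference?** Section 2.3.1 gives "The calculations assumed 80% power", "a two-sided significance level of 0.05", "standard deviation *σ* = 1.39" and "effect size *Δ* 0.17". The standard two-mean formula before clustering is

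n = 2σ²(1.96 + 0.842)²/Δ² = 2 × 1.39² × 7.849/0.17² ≈ 1,050 per arm.

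The formula as printed, with (2σ²)² in the numerator, gives about 4,055 at a design effect of 1. Neither returns 180. Before clustering, power for 0.17 is about 21% with 180 per arm, 23% with 200 and 19% with 160. No value of the intracluster correlation ρ or of m is stated, so the design effect cannot be computed from the article.

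**The case against.** A reader might infer that the plan's rules make 180 unattainable. The article does not support that. Enrolling 200 and losing 10%, the lower end of the plan's own range, leaves exactly 180. The 150 is a minimum, and a larger school can supply 200. What holds is that 180 is not guaranteed.

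Four further points can be made for the plan.

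- **The floor may not bind.** Section 2.1 says the study commenced in March 2026, and section 2.2 reports the eligibility criteria in the past tense. The schools may already be known and large enough. Their rolls are not given, so no actual shortfall is shown. This stands; the criticism is of the stated purpose of the floor, not of any particular school.
- **Children lost to follow-up are not all lost to analysis.** The mixed model in section 2.6.2 uses both T1 and T2, so a child seen at T1 but not at T2 still contributes. This stands; 152 and 160 count children completing follow-up and equal the analysed number only if every loss precedes T1.
- **The effect on power is small.** Going from 180 to 160 per arm moves nominal power from about 21% to about 19%, and adding pupils does not reduce uncertainty between two schools. This is fair. It limits the statistical consequence, but the stated allowance is still wrong.
- **Raising the floor is not merely editorial.** In a trial under way it would alter a school eligibility criterion. This stands and shapes the fix.

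**Conclusion.** The concern holds in this form. An enrolment of 190–200 per school preserves the stated 180 only up to 5.3% loss (from 190) or 10% loss (from 200); the stated 10–20% would need 200–225. With 200 per group, 160 per school complete follow-up at 20% loss, and 152 from 190. The 150-pupil floor does not ensure an adequate cluster size, being below both the 180 required and the 200 to be enrolled. The plan falls short of 180 whenever attrition exceeds 10%, or when a selected school has too few eligible, consenting pupils.

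The attrition result rests only on the article's own figures and simple proportional loss. The floor figures of 135 and 120 also assume that every pupil is eligible and consents, which is the favourable case.

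Taking 180 as the reference does not endorse it. It does not follow from the stated standard deviation, difference, significance level and power, so correcting the attrition step would not produce 80% power. That is a separate and larger problem.

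**What to change.** 1. In section 2.3.1, restate the allowance as up to 10% attrition at 200 enrolled (about 5% at 190), and report the number expected to complete follow-up at 20% loss: 160 per school. If the 10–20% allowance is to be kept, the target must instead read 200–225 per school, and the total of 400 in section 2.3 must change to match.
2. In section 2.2, remove the claim that the 150-pupil floor ensures sufficient size. Alternatively, if schools have not yet been selected, align the floor with the enrolment target and leave room for non-consent and exclusions.
3. If the schools are already chosen, leave the criterion as it was applied, and state their actual grade 3–4 rolls and the achievable number per school.
4. Correct the derivation of 180 separately, and carry any new figure through the attrition step.

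Item 1 as an allowance restatement, item 3 and the removal option in item 2 are text corrections; their price is a less favourable stated attrition tolerance. Raising the target or the floor in a trial that has commenced would be a design change.

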#### Inclusion criteria

2.3.2

Children enrolled in grades 3–4 in the specified region will be eligible provided that written informed consent is obtained from a parent or guardian. To ensure safety and feasibility, participants must be in good general health, excluding those with severe acute or chronic conditions that would prevent full participation in standard school activities.

#### Exclusion criteria

2.3.3

Students will be excluded if they: (1) Had diagnosed allergies or intolerances to coarse cereals, and (2) Had chronic diseases confirmed by a secondary hospital or higher (eg. type 1 diabetes, congenital heart disease) that could affect dietary intake, metabolism or growth.

### Intervention strategies

2.4

#### Intervention group

2.4.1

Eligible students aged 8–12 years (grades 3–4) in the intervention school received daily coarse-cereal intervention incorporated into school meals, combined with structured nutrition education for students and parents.

#### Coarse-cereal substitution in school meals

2.4.2

##### Coarse-cereal substitution

2.4.2.1

According to the Dietary Guidelines for Chinese Residents (22), children aged 7 ~ 13 years should consume 30–70 g of coarse cereals or legumes daily. In the intervention school, approximately 50 g of coarse cereals per student per day will be provided through the substitution of refined grains in school meals. This target amount is within the recommended range and will be integrated into breakfast, lunch, and dinner (the latter for boarding students only).

To ensure dietary diversity and palatability, the research team, in collaboration with school kitchen staff, developed a standardized coarse-cereal menu. The intervention will utilize common types of coarse cereals and legumes such as oats, brown rice, buckwheat, millet, corn grits, red beans, and mung beans. Over 100 dishes across 12 categories (e.g., buckwheat noodles, red bean rice, millet congee, oat steamed bread) were created, with menus designed to rotate weekly. The core substitution method is a direct, gram-for-gram replacement: coarse cereals will constitute a portion of the staple food, for instance, by using brown rice to partially or wholly replace white rice, or by incorporating whole wheat/oat flour into wheat flour for making buns and noodles. Each daily menu is designed to provide approximately 50 g of coarse cereals and about 4 g of dietary fiber per student, based on calculations from the China Food Composition Tables.

A registered dietitian will audit the school meal menus every 2–3 days to verify coarse-cereal types, portion sizes, and rotation frequency. Coarse cereals will be prepared by steaming, boiling, or stewing to minimize nutrient loss. Recipes were adjusted after pilot testing to balance nutrient content and student acceptance to optimize compliance.

#### Multi-level nutrition education

2.4.3

##### Student education

2.4.3.1

Students will attend 7 structured, interactive nutrition education sessions (approximately 45 min each, conducted twice per month). These sessions will be delivered by trained school health teachers or homeroom teachers using a standardized curriculum developed by the research team. The curriculum covers sequential topics including: (i) Introduction to Coarse Cereals and Their Nutritional Value; (ii) The Food Guide Pagoda and Building a Balanced Diet; (iii) Understanding Obesity and Its Health Risks; (iv) Making Healthy Snack and Beverage Choices; and (v) Practical Activities (e.g., comparing brown and white rice, designing a healthy lunch box). To ensure consistency and quality, teachers will receive a two-hour training workshop and a detailed lesson plan kit prior to the intervention. Research assistants will conduct random spot checks (via classroom observation or lesson recording review) to monitor fidelity to the protocol.

##### Parent engagement

2.4.3.2

Parents or guardians will receive nutrition education through two WeChat messages per month (totaling six sessions) sent via class group chats. The messages will cover practical topics such as home cooking methods for coarse cereals, interpreting nutrition labels, and preparing healthy after-school snacks. Additionally, four live webinars focusing on child nutrition and weight management will be hosted by project nutritionists and scheduled on weekday evenings to maximize accessibility. To encourage home environment support, school principals and teachers will also receive summarized briefings on the key messages. Parent engagement will be monitored through metrics such as message read-receipt rates and webinar attendance logs.

##### Control group consideration

2.4.3.3

To maintain ethical rigor, the control group will not receive any active nutrition education during the 6-month intervention period. Upon study completion, they will be provided with access to the compiled educational materials (e.g., lesson recordings, digital resources).

#### Control group

2.4.4

Students in the control schools will continue to receive standard school meals without coarse-cereal substitution and will not receive any nutrition education during the intervention and follow-up periods. To ensure ethical rigor, the control group will be provided with access to the same educational materials (including lesson recordings, lesson plans, and digital resources) upon completion of the 6-month follow-up.

### Data collection

2.5

Data will be collected at three time points: baseline (T0), post-intervention at 3 months (T1), and at 6-month follow-up (T2, 9 months). The specific time points for each category of data collection are detailed in Figure 2.

**Figure 2 fig2:**
[figure not shown]
Data collection timeline for coarse-cereal intervention study.

#### Exposure indicators

2.5.1

These indicators will quantify actual coarse-cereal intake in the intervention group, assess adherence to the 3-month intervention, and compare intake levels with the control group’s usual diet.

##### 3-Day 24-hour dietary recall (3D-24HR)

2.5.1.1

Students recorded all food and beverage intake over three consecutive days (two weekdays, one weekend) at T0, T1, and T2. Kitchen scales will be provided to measure portions, and cooking methods will be recorded. Canteen staff documented daily menus to calculate in-school coarse-cereal intake. Parents maintained weekly coarse-cereal purchase and cooking logs. Daily intake (g/day) will be calculated using the China Food Composition Tables.

